### Data collection

A nurse practitioner or clinical investigator (depending on the local organization of the participating hospital) will be responsible for the pre-operative and post-operative data collection. The surgeon who performed the ALND will be responsible for the peri-operative data collection. Data will be stored anonymously under a unique trial number. The principal investigators (EL and PG) will have access to the data. All data will be collected in an online case report form and an online participant questionnaire (PQ). The timetable and source of the data collection is listed in Table 1.

**Table 1 T1:** Data collection

**Data**	**Source**	**Pre-operative**	**Peri-operative**	**Follow-up at 6, 12, and 24 months**
Baseline characteristics	CRF	x		
Medical history	CRF	x		
Pre-operative tumor status/markers	CRF	x		
Operation data including:	CRF		x	
Registration				
Randomization				
Post-operative complications	CRF/PQ	x^a^		x
Quality of life	PQ			x
Axillary recurrence rate	CRF			x

CRF, case report form; PQ, participant questionnaire.

^a^The volume, circumference and mobility of the arm will be measured pre-operatively.

### Blinding

The qualified oncologic breast surgeon will perform the procedure and therefore cannot be blinded. The patient and the person responsible for the post-operative data collection and measurements will not be aware of the performed procedure (double-blind procedure).

### Statistics

#### Sample size

The clinically relevant amount of lymphedema is stated as a volume difference of 200 ml or more between both arms. Primary research shows that the risk of BCRL is 15% in patients undergoing an ALND. It is expected that ARM-ALND will reduce the risk to 5%. Based on these assumptions, we will need to study 140 subjects in the standard ALND group and 140 subjects in the ALND-ARM group to be able to reject the null hypothesis that the failure rates for experimental and control subjects are equal with a probability (power) of 0.8. The Type I error probability associated with this test of the null hypothesis is 0.05.

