## Methods/design

The aim of the ARM trial is to determine the usefulness of the ARM technique in identifying and sparing the upper limb-related axillary LNs, and its ability to reduce the risk of lymphedema of the upper limb. After determining the indication for a cALND basis on a tumor-positive SLN, patients will be randomly allocated to one of two groups: ALND with preservation of the upper limb-related axillary LNs (ARM-ALND) and a level I-II ALND (standard ALND).

Patients who are candidates for a primary axillary lymph node dissection (pALND), based on axillary metastases proven by pre-operative cytology, can be included in the registration study to confirm the feasibility of the procedure and to perform a further subgroup analysis. A schematic overview of the trial is given in Figure 1.

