### Randomization

Randomization will be performed using a web-based randomization system, and will be stratified by center. This randomization application and the internet-based help service will be available 24 hours a day, 7 days a week. Because of practical considerations, the randomization will take place as soon as the patient has given written informed consent. Based on our previous experience with the ARM procedure, we expect that identification or preservation of the ARM nodes/lymphatics will not be possible in 5 to 15% of the randomized patients. In such cases, the standard ALND will be performed, if possible, and the ARM nodes/lymphatics will be separately removed and sent for analysis. These patients will be included in the analysis in accordance with the intention-to-treat principle, but excluded from the sensitivity analysis. (Figure 1) (more information can be found at http://www.armstudie.nl).

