### Interventions

Surgeons familiar with the ARM procedure will perform the ALND. In our feasibility study (Amphia Hospital Breda, the Netherlands), the learning curve for performing the ARM procedure was very small (barely measureable), and the overall identification rate of the upper-limb LNs was up to 94%. Based on these results, we consider an oncologic breast surgeon should be capable of performing an ARM procedure once they have performed five procedures under the supervision of one of the oncologic surgeons (EL or PG) from the Amphia Hospital Breda.

The procedure will be performed under general anesthesia. For the procedure, approximately 2 ml of blue patent V dye (Laboratoire Guerbet, Aulnay-sous-Bois, France) from a stock solution of 25 mg/ml is injected subcutaneously into the inner arm, along the medial intermuscular groove of the ipsilateral arm. This dye is identical to the dye used to perform an SLNB. After injection, the site of injection is massaged and the arm elevated for a few minutes to enhance lymphatic drainage of this limb. Next, the patient is covered with sterile drapes, and the ALND can be started.

The technical part of the operation is identical to a normal level I to II ALND, except for the first part of the operation. After incision, the blue-stained LNs and lymphatics are identified. In the ARM-ALND group, the blue-stained LNs and lymphatics will be spared, then a normal ALND will be performed. In the standard ALND group, a normal ALND will be performed without sparing the upper-limb lymphatics and LNs. The pathologist will separately analyze the LNs (level I to II nodes and ARM nodes, Figure 2).

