### Ethics

Patient recruitment will start in April 2013 in seven breast-cancer centers in the Netherlands. The study will finish enrolment as soon as 280 patients are included, and is expected to finish by April 2016. Collection and analysis of the results will be performed in the following 2 years.

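### The sample size of 280 has no reserve for the plan's own expected 5–15% preservation failures or for loss by 24 months; if 5% is the risk with preservation achieved, intention-to-treat power is about 63–75%, not 80%

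*Protocol article*

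**What the plan says.** The Sample size section sets the control risk ("Primary research shows that the risk of BCRL is 15% in patients undergoing an ALND") and the target ("It is expected that ARM-ALND will reduce the risk to 5"%). With a type I error of 0.05 it concludes that "we will need to study 140 subjects in the standard ALND group and 140 subjects in the ALND-ARM group" to reject the hypothesis that the rates are "equal with a probability (power) of 0.8". Data analysis specifies an uncorrected chi-square test and makes 24 months the primary time point.

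Three other sections bear on this calculation:

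- Methods/design describes the experimental arm as "ALND with preservation of the upper limb-related axillary LNs (ARM-ALND").
- Randomization says: "we expect that identification or preservation of the ARM nodes/lymphatics will not be possible in 5 to 15% of the randomized patients". Those patients are to have standard ALND where possible, with the ARM nodes removed separately. They stay in the intention-to-treat analysis and are left out only of a sensitivity analysis.
- Ethics says: "The study will finish enrolment as soon as 280 patients are included".

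The Sample size section mentions neither the expected failures nor loss to follow-up. No attrition rate appears anywhere in the article.

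**The concern.** The calculation contrasts 15% with 5%, as if everyone allocated to ARM-ALND had the benefit of preservation and everyone enrolled were measured at 24 months. The Randomization section says that the first condition is not expected to hold. Patients in the ARM arm whose nodes cannot be preserved have the same operation as the controls, so keeping them in that arm, as intention-to-treat requires, narrows the contrast. Stopping at 280 enrolled also means that any death, withdrawal or missed 24-month measurement comes straight out of the number the calculation needs.

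If the true power is clearly below 80%, a real reduction in lymphedema is more likely to be missed than the article tells its readers. A null result could then be over-read as evidence that ARM does not help.

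**Working it through.** **Inputs from the article.** Control risk p1 = 0.15, ARM risk 0.05, power 0.80, alpha 0.05, 140 per arm (Sample size); uncorrected chi-square, 24 months (Data analysis); failure rate f = 0.05 to 0.15 (Randomization); enrolment ends at 280 (Ethics). Sidedness is not stated. The two-sided formula reproduces 140, whereas one-sided gives 111 per arm and two-sided with continuity correction gives 160.

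**Inputs assumed.** (a) The 5% is the risk when preservation succeeds. (b) Failures in the ARM arm carry the 15% control risk. (c) Loss by 24 months is d = 0, 10% or 20%, equal in both arms. The article gives no figure for loss, so a range is shown.

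**Step 1: reproduce the plan's figure.**

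n per arm = [1.96·√(2·0.10·0.90) + 0.8416·√(0.15·0.85 + 0.05·0.95)]² / 0.10² = (0.8316 + 0.3521)² / 0.01 = 140.1.

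Power at n per arm = Φ{ [(p1 − p2)·√n − 1.96·√(2·p̄·(1 − p̄))] / √[p1(1 − p1) + p2(1 − p2)] }, where p̄ is the mean of p1 and p2.

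At n = 140 and p2 = 0.05: (1.1832 − 0.8315)/0.4183 = 0.841, so power is 79.97%. The exact binomial power of the uncorrected chi-square test is 81.4%. The stated figure is reproduced, with no planned reserve.

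**Step 2: dilution by failures, no loss.** ARM-arm risk p2 = 0.05(1 − f) + 0.15f. Failures in the standard arm change nothing, because those patients have standard ALND anyway.

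Example, f = 0.10: p2 = 0.06 and p̄ = 0.105; (0.09·11.832 − 1.96·√0.18795)/√0.1839 = 0.2152/0.4288 = 0.502, so power is 69.2%.

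**Step 3: add assumed loss.** n = 140(1 − d), that is 126 per arm at 10% and 112 at 20%.

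Power by normal approximation, exact power in brackets:

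| Failure rate f | ARM-arm risk | No loss (140) | 10% loss (126) | 20% loss (112) |
|---|---|---|---|---|
| 0 | 5.0% | 80.0% (81.4%) | 75.7% (77.7%) | 70.6% (73.5%) |
| 5% | 5.5% | 74.8% (76.1%) | 70.3% (72.0%) | 65.1% (67.7%) |
| 10% | 6.0% | 69.2% (70.2%) | 64.6% (66.0%) | 59.5% (61.7%) |
| 15% | 6.5% | 63.3% (64.1%) | 58.7% (59.8%) | 53.8% (55.7%) |

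The row f = 0 also covers the other reading, in which 5% is already the as-randomized risk. Only loss then reduces power.

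**Step 4: size needed for 80%.** With failures of 5, 10 and 15% and no loss, the normal approximation needs 159, 181 and 208 per arm.

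**The case against.** **The 5% may already be an as-randomized risk.** The Sample size section does not say. The definition in Methods/design favours the preserved-patient reading but does not settle it. If 5% already averages over failures, the dilution in step 2 disappears. This stands, and it is why both readings are shown.

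**Failures may not carry the full control risk.** The article does not state their risk, and it says standard ALND is done where possible. At an illustrative 10% risk among failures, exact power with no loss is 73–79%. The direction is unchanged; the size is smaller.

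**The full protocol may hold an attrition allowance.** An article condenses. But this one reports the whole calculation and its result, 280 is the uninflated figure, and enrolment ends at 280 included.

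**A sensitivity analysis without failures is planned.** It helps in interpreting a null result, but it does not change the power of the intention-to-treat comparison.

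**Stronger readings that the article does not support:**

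- *Power is really about 55%.* That needs 15% failures together with roughly 15–20% loss, and no loss rate is given.
- *80% requires that not a single patient is lost.* With no dilution, exact power is still 80.1% at 133 per arm, a 5% loss.
- *The pilot shows a 14% failure rate in this trial's population.* Background gives visualization rates of 86% and 94% for 50 SLN-positive and 43 cytology-positive patients respectively. But 94% is not attainable with 43 (40/43 = 93.0%, 41/43 = 95.3%). The reported P = 0.196 is reproduced by 37/43 against 47/50, so the group sizes and rates conflict. Interventions adds that "the overall identification rate of the upper-limb LNs was up to 94"%. Until these statements are reconciled, neither rate can be assigned to SLN-positive patients. A 14% rate would in any case lie inside the 5–15% already used.
- *Randomization is timed wrongly.* The article gives practical reasons for randomizing at consent, and the point does not depend on changing that.

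**Conclusion.** The concern holds in this form: the sample-size arithmetic is correct, but it rests on an undeclared planning assumption that sits badly with the article's own Randomization section. The 80% applies to an as-randomized contrast of 15% versus 5% with essentially all 280 patients measured at 24 months.

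Under assumptions (a) and (b), the article's own failure range lowers power to about 63–75% (exact 64–76%) before any loss. The chance of missing the planned effect becomes about 25–37% instead of 20%. An assumed 10% loss takes power to about 59–70% (exact 60–72%). If 5% is already the as-randomized risk, the shortfall comes from loss alone: about 76% at an assumed 10% loss and 71% at 20% (exact 78% and 74%).

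**What to change.** In the Sample size section:

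1. State whether 5% is the risk as randomized or the risk in patients whose nodes are preserved. If the latter, state the risk assumed for failures.
2. State the assumed non-preservation rate, consistent with the 5–15% under Randomization, and the assumed attrition by 24 months.
3. Restate the power that 280 enrolled patients give. On the preserved-patient reading this is about 69% at 10% non-preservation with no loss, and about 65% with an assumed 10% loss.

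Separately, reconcile the pilot group sizes and rates in Background with each other and with the overall rate under Interventions before using any of them to support the non-preservation rate.

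This changes wording only and needs no extra patients; the cost is a less favourable stated power. If the trial wishes to keep 80%, the alternative is to recompute the sample size, at 159–208 per arm before loss on the preserved-patient reading.

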#### Data analysis

We will use an uncorrected χ^2^ statistic to test the null hypothesis for the proportion of patients developing lymphedema in the upper limb. These tests will be performed after 6, 12, and 24 months. We are interested in the course of the development of lymphedema, based on the measurements at each of the three specified time points. As development of lymphedema has been reported to occur 2 or more years after surgery, the measurement of lymphedema at 24 months is considered our primary endpoint.

To compare continuous data, such as pain and quality of life, analysis of covariance (ANCOVA) will be performed, using baseline values as a covariate. Separate analyses will be performed for the three time points (6, 12 and 24 months). The local recurrence rate in both groups will be analyzed by the Kaplan-Meier method and compared with the log-rank test. A repeated-measures analysis will be performed to compare the changes in continuous data between the two groups, until 2 years after treatment. It is expected that not only will the prevalence of lymphedema be higher in the standard ALND arm, but also that it will occur earlier and will be more severe. To test this hypothesis, interaction terms between treatment and time will be included in the repeated-measures analysis.

All data will be documented and analyzed using SPSS software (SPSS Inc., Chicago, IL, USA), with the exception of the repeated-measures analysis, for which SAS software (SAS Institute, Cary, NC, USA) with the procedure PROC MIXED. No interim analysis will be performed.

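### The primary chi-square ignores the center stratification used in randomization; if lymphedema rates differ between centers, the test is mildly conservative and forgoes a little power

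*Protocol article*

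**What the plan says.** Under Randomization, the protocol article says that allocation "will be stratified by center". Under Data analysis it prescribes an uncorrected χ² "statistic to test the null hypothesis for the proportion of patients developing lymphedema in the upper limb", applied at 6, 12 and 24 months. It then singles out one time point: "the measurement of lymphedema at 24 months is considered our primary endpoint". No stratified or center-adjusted version of this test is named.

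Under Sample size, the planning rates are 15% with standard ALND and 5% with ARM-ALND, at a type I error of 0.05 and power of 0.8: "we will need to study 140 subjects in the standard ALND group and 140 subjects in the ALND-ARM group".

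The number of centers is five in the Abstract and under Settings and location, and seven under Ethics. No section gives lymphedema rates or expected patient numbers by center.

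**The concern.** Stratified allocation balances the two arms within each center, so differences between centers cancel out of the treatment comparison. The pooled chi-square does not use this. Its variance is built from the overall event rate and still counts between-center variation as error. If center rates differ, the estimated standard error is therefore larger than the true one. The real type I error then falls below the stated 0.05, and some power is given up that a test following the randomization strata would keep.

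The protocol names its primary test explicitly, so this is a choice it has made and not a detail left to an analysis plan. What is at stake is efficiency. The error lies on the conservative side and cannot create a false positive.

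**Working it through.** **Inputs from the document.** Control rate 15%, ARM-ALND rate 5%, 140 per arm, type I error 0.05, power 0.8 (Sample size); uncorrected chi-square, 24 months primary (Data analysis); strata are centers (Randomization); five centers (Settings and location).

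**Assumptions.** Two-sided test (sidedness is not stated), equal centers with 28 patients per arm in each, and the center-specific control rates listed below, each set averaging 15%.

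**1. The plan's own figure.** With a mean rate of 0.10,

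n = [1.96·√(2·0.10·0.90) + 0.8416·√(0.15·0.85 + 0.05·0.95)]² / 0.10² = (0.8315 + 0.3521)² / 0.01 ≈ 140.1, or 141 when rounded up.

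At 140 per arm the normal-approximation power is 79.97%. The stated 140 therefore reproduces, and it matches the unstratified, uncorrected, two-sided test. A continuity correction would give 160, and a one-sided test 111.

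**2. Why the pooled test is conservative.** Let p_c be the center rates under the null and p their mean. Then

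p(1−p) = mean of p_c(1−p_c) + variance of p_c.

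The pooled chi-square uses the left side. With allocation balanced within center, the true variance involves only the first term on the right. The real type I error is therefore about 2·[1 − Φ(1.96·√R)], where R = p(1−p) / [p(1−p) − variance of p_c].

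Example with center rates 5, 10, 15, 20 and 25%:
- variance of p_c = (0.01 + 0.0025 + 0 + 0.0025 + 0.01)/5 = 0.005
- p(1−p) = 0.15·0.85 = 0.1275
- R = 0.1275/0.1225 = 1.0408, and √R = 1.0202
- 1.96·1.0202 = 2.000, so the type I error is about 0.0455.

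**3. Size of the effect.** The table compares the uncorrected chi-square with the center-stratified Cochran-Mantel-Haenszel (CMH) test in 400,000 simulated trials per row. For type I error both arms have the control rates. For power the risk ratio is 1/3 in every center, so the overall rates stay at 15% v 5%.

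| Center control rates (%) | Type I error by formula, chi-square | Type I error simulated, chi-square v CMH | Power (%), chi-square v CMH | Power forgone (points) |
|---|---|---|---|---|
| 15 in all | 0.050 | 0.051 v 0.050 | 81.5 v 81.7 | 0.2 |
| 10, 12.5, 15, 17.5, 20 | 0.049 | 0.049 v 0.049 | 81.5 v 81.9 | 0.4 |
| 5, 10, 15, 20, 25 | 0.046 | 0.046 v 0.050 | 81.8 v 82.8 | 1.0 |
| 5, 5, 10, 20, 35 | 0.039 | 0.039 v 0.050 | 82.3 v 84.3 | 2.0 |
| 2, 5, 8, 20, 40 | 0.033 | 0.034 v 0.049 | 82.8 v 85.5 | 2.7 |

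For a spread of 3-39% with the same mean, simulation gave a type I error of 0.036 v 0.050 and about 2.7 points forgone. Simulated power with equal rates (81.5%) is a little above the normal approximation (79.97%).

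**4. Number of centers.** Seven equal centers with control rates of 5-25% give a type I error of 0.046 v 0.050 and power of 81.7% v 82.6%. The five-or-seven discrepancy does not change the result.

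**5. A different effect model.** If the odds ratio is held constant instead of the risk ratio, chi-square v CMH power is 80.1% v 81.2% (5-25%), 77.9% v 80.4% (5-35%) and 75.8% v 79.5% (2-40%). In the last two cases the overall ARM-ALND rate has drifted up to about 5.4% and 5.6%, so the planned 15% v 5% no longer holds.

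**The case against.** The case for leaving the test alone is respectable. The planned test is valid and the sample size was calculated for it. The premise that center rates differ is not documented. Several features point towards uniformity: surgeons complete supervised procedures before taking part, the sites are dedicated breast-cancer centers in one country, and lymphedema is defined by comparing a patient's two arms with a named volume meter. At moderate spreads the gain from stratifying is 1 point or less. All of this stands, and it limits the size of the point. It does not show that the pooled test is the better choice: CMH power was higher in every scenario, even slightly so with equal rates.

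Three stronger readings are tempting but not supported.

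- A reader might infer that the chi-square takes the trial below its stated 80% power. The constant-odds-ratio figures of 77.9% and 75.8% seem to show this. Much of that fall comes from the smaller overall treatment difference, and it affects both tests: at 5-35%, moving from a constant risk ratio to a constant odds ratio lowers the chi-square from 82.3% to 77.9% and CMH from 84.3% to 80.4%. With 15% v 5% held, chi-square power stays above 81%.
- A reader might take the 7 to 77% range in the Background as evidence of center differences. It is a spread across published studies, which the text links to radiotherapy and to the definition used. It says nothing about these centers.
- A reader might fault the covariance and repeated-measures analyses for not naming center. The article does not say that baseline is the only covariate, and such model detail is commonly left to the full protocol or analysis plan.

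**Conclusion.** The mismatch is real and stated in the text: allocation is stratified by center and the primary test is not. Its consequence is conditional and small. If center rates differ, the chi-square is mildly conservative and forgoes power relative to a stratified test: about 0.4 points at control rates of 10-20%, 1 point at 5-25%, and 2-3 points at 5-35% or 3-39%. The corresponding type I errors are about 0.05, 0.046 and 0.036-0.040.

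The direction is secure. The size rests on assumed center rates, equal center sizes and overall rates of 15% v 5%. This is a gain forgone and not a shortfall against the stated power, and a significant result from the planned test would stand. The point is minor.

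**What to change.** In Data analysis, make the primary 24-month comparison a Cochran-Mantel-Haenszel test stratified by center, with a prespecified rule for pooling very small centers. Report a Mantel-Haenszel risk difference with its 95% CI, and keep the uncorrected chi-square as a supportive analysis, which preserves the link to the sample size calculation. Fix the change before unblinding.

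The cost is a line or two of wording. It needs no more patients and no new data, and the sample size stays at 140 per arm. Adding center to the secondary models would be consistent with the design, but it is optional and not part of this point.

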### Primary and secondary outcome measures

The primary outcome will be the occurrence of lymphedema in the upper limb. Lymphedema will be measured s at 6, 12 and 24 months, using the following two techniques.

1) The water-displacement method. This method is regarded as the gold standard for the measurement of lymphedema. For the assessment of upper-limb volume, an arm volume meter will be used (NV Varitex Haarlem, The Netherlands). This method has high reproducibility [17]. Both upper limbs will be measured pre-operatively and post-operatively. Lymphedema is defined as a difference in limb volume of greater than 200 ml between the treated and untreated side, as described by Lopez Penha *et al*. [18].

2) Circumference method. The arm circumference will be measured at four sites: metacarpophalangeal joints, wrist, 100 mm distal from the lateral epicondyle, and 150 mm proximal of the epicondyle. A difference of more than 20 mm between the affected and contralateral arm is considered clinically significant.

The secondary endpoints will be measured at 6, 12, and 24 months and comprise the following:

1) Paresthesia/numbness. This will be assessed with the aid of a standardized questionnaire developed for patients with breast cancer [19].

2) Pain. This will be measured using a visual analog scale.

3) Loss of shoulder mobility. The shoulder function of the affected upper limb will be compared with the unaffected one. Loss of abduction of more than 20 degrees will be considered abnormal.

4) Quality of life. This will be assessed by a standardized questionnaire developed for patients with breast cancer [21]. This large questionnaire includes the WHOQOL-Bref.

5) Locoregional recurrence rate: This will be assessed by a physical examination during follow-up. In cases where there is suspicion of recurrence, ultrasonography (with or without biopsy) will be performed.

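### The planned ANCOVA of pain and quality of life adjusts for baseline, but the data-collection schedule shows no pre-operative quality-of-life assessment and probably no pre-operative pain score

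*Protocol article*

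**What the plan says.** For continuous data, with pain and quality of life as its examples, the Data analysis section states: "analysis of covariance (ANCOVA) will be performed, using baseline values as a covariate". It adds: "Separate analyses will be performed for the three time points (6, 12 and 24 months"). It also plans a repeated-measures comparison of changes in continuous data up to two years.

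The Primary and secondary outcome measures section lists pain and quality of life among the secondary endpoints. For pain it says "This will be measured using a visual analog scale"; for the quality-of-life instrument, "This large questionnaire includes the WHOQOL-Bref". The list is introduced by "The secondary endpoints will be measured at 6, 12, and 24 months and comprise the following".

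Table 1 in the Data collection section has a pre-operative, a peri-operative and a follow-up column. The quality-of-life row, with the participant questionnaire as source, is marked under follow-up only. The row for post-operative complications, with case report form and participant questionnaire as sources, is marked both pre-operatively and at follow-up. A footnote to its pre-operative mark reads: "The volume, circumference and mobility of the arm will be measured pre-operatively". The Research question section counts pain among the secondary post-operative complications, so pain belongs to that row.

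**The concern.** The analysis text presupposes a baseline value for the two outcomes it names as examples. The article's own collection table gives none for quality of life and, read naturally, none for pain. This is a conflict between two explicit statements, not a detail left to a fuller document.

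Research question 2 asks about quality of life, and pain is a named secondary complication. If the table is what sites follow, the specified model has no covariate for quality of life and probably none for pain. Change from baseline then cannot be computed for an outcome without a baseline, and chance imbalance at baseline can be neither seen nor adjusted for. A pre-operative score cannot be recovered after the axillary operation, so the gap has to be closed before patients pass that point.

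**Working it through.** **1. Schedule against analysis, outcome by outcome**

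| Outcome | Baseline needed by the Data analysis section | Pre-operative entry in Table 1 |
|---|---|---|
| Quality of life | Yes, named | None; the row is marked at follow-up only |
| Pain (visual analog scale) | Yes, named | The row is marked, but the footnote names only volume, circumference and mobility |
| Arm volume, circumference | Yes, if analysed as continuous data | Yes, by the footnote |

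The baseline-characteristics row does not fill the gap for quality of life. Its source is the case report form, whereas quality of life has its own row with the participant questionnaire as source.

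**2. The plan's own sample size**

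Inputs from the Sample size section: 15% versus 5%, power 0.8, alpha 0.05. The uncorrected chi-square test is from the Data analysis section. Sidedness is not stated, so two-sided is assumed.

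n per arm = [1.960 × √(2 × 0.10 × 0.90) + 0.842 × √(0.15 × 0.85 + 0.05 × 0.95)]² / 0.10²

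= [0.8315 + 0.3521]² / 0.01 ≈ 140.1, or 141 rounded up.

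The plan states 140, and power at 140 per arm is 0.7997. The figure reproduces. It rests on binary lymphedema alone, so a missing baseline for pain or quality of life does not touch it.

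**3. Precision lost on the secondary outcomes**

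With a baseline covariate whose correlation with follow-up is r, ANCOVA leaves a fraction 1 − r² of the outcome variance. The documents give no r; 0.3, 0.5 and 0.7 are assumptions that span a range.

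Detectable standardised difference = (1.960 + 0.842) × √(2/140) × √(1 − r²) = 0.335 × √(1 − r²)

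| r (assumed) | 1 − r² | Detectable difference (SD) |
|---|---|---|
| No covariate | 1.00 | 0.335 |
| 0.3 | 0.91 | 0.319 |
| 0.5 | 0.75 | 0.290 |
| 0.7 | 0.51 | 0.239 |

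These figures assume that all 140 patients per arm are observed at the time point concerned.

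**The case against.** Several stronger readings are tempting, and the text does not support them.

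- **That the outcome section independently proves there is no baseline.** A reader might infer this from "The secondary endpoints will be measured at 6, 12, and 24 months". The same list includes shoulder mobility, which the Table 1 footnote says is measured before surgery. Lymphedema is likewise given three follow-up times, yet both limbs are measured pre-operatively. The wording lists follow-up visits and does not exclude a baseline, so the evidence is Table 1 and its footnote.
- **That pain is as certain a gap as quality of life.** The complications row does carry a pre-operative mark, and the footnote does not say that its list is complete. Reading it as complete is natural, but it is an inference.
- **That baseline data will definitely not be collected.** The article shows two statements in conflict. If the full protocol does collect these scores before surgery, Table 1 is the part that is wrong. Either way the two must be reconciled.
- **That the comparison is invalid or research question 2 cannot be answered.** Randomisation keeps the unadjusted comparison of follow-up means unbiased. Change between 6, 12 and 24 months, and the treatment-by-time interaction over those visits, can still be estimated. Only change from baseline is lost. The interaction hypothesis in the Data analysis section concerns lymphedema, and arm volume has a baseline.

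It is also fair to say that the trial is not sized on pain or quality of life, and that the loss is slight if r is low. What stands after all this is a real mismatch between schedule and analysis, firm for quality of life and probable for pain.

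**Conclusion.** The point holds as an internal inconsistency that affects secondary outcomes. On the schedule as printed, the baseline-adjusted ANCOVA and any change-from-baseline analysis cannot be done as stated for quality of life. The same applies to pain if the footnote is read as complete.

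The consequence is lost precision, not bias. The detectable difference rises from 0.319, 0.290 or 0.239 SD to 0.335 SD, depending on whether the correlation is 0.3, 0.5 or 0.7. Those correlations are assumptions and do not come from the documents. The primary chi-square test, the sample size and any baseline-adjusted analysis of arm volume or circumference are unaffected.

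**What to change.** Add a pre-operative mark in Table 1 for the quality-of-life part of the participant questionnaire and for the pain visual analog scale, and say the same in the Primary and secondary outcome measures section. Both should be completed after consent and before randomisation, or at least before surgery. The Randomization section has allocation follow as soon as consent is given, so completion before it must be planned into the consent visit. Patient blinding gives some protection if the form is completed later but still before surgery.

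If any patients are already enrolled without a baseline, keep one model for all patients and prespecify how missing baselines are handled, for example mean imputation of the baseline or a missing indicator. The covariate cannot be dropped for some patients within a single ANCOVA.

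If baseline values will not be collected at all, remove the baseline covariate for these outcomes from the Data analysis section.

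The cost is one additional completion of an existing online questionnaire and a pain score per patient, plus a minor amendment. A pre-operative data-collection contact is already planned.
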